## **1. SUMMARY**

The project is innovative in its research question and has the following foci:

A basic science-oriented part on visual and cortical processing of Chinese characters, and an application-oriented linguistic and pedagogical part of social relevance.

It is thus an interdisciplinary project and includes the following specialties: Ophthalmology, Neuro-Ophthalmology, Neuro-Sensory Science, Sinology, Linguistics, Pedagogy.

Dyslexia is a common developmental disorder of reading and writing (4-5% of German school children). Those affected are severely disadvantaged at school and in professional life, often resulting in psychological and social sequelae.

Research to date has mainly examined the children's deficits, while little attention has been paid to their strengths, especially their visual abilities.

In our research, German-speaking dyslexic children were found to have problems only with the written language stimuli, whereas pictorial material (pictograms) was processed equally well as in non-dyslexic children. Therefore, it will be investigated for the first time whether German-speaking dyslexic children can learn the non-letter logographic Chinese script as well as their normal-reading classmates, and how the characters are processed visually.

Twenty-four children each from 4th and 5th grade with and without dyslexia will be included in the study, 3 each in the pilot study.

A detailed analysis of the fixations on the characters by means of a scanning laser ophthalmoscope, which allows the reading process to be recorded directly on the retina, should provide important information about the type of processing (local or global). Magnetoencephalography will also be used to examine cortical processing.

The children will then receive a 24-hour block of Chinese lessons, for which the teaching material will be developed in a child-friendly manner.

It will be of interest to see how characters are learned in both groups and whether the dyslexics benefit.

If this were the case, dyslexic children could gain an advantage in school and their working life through the special language skills and would not have to be the "eternal losers" as they have been up to now. It could also have a positive impact on their self-confidence and their psychological and social development.

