### Processing of stimuli in the brain

The cortical processing of the stimuli (letters versus pictograms) takes place in different brain areas, as we found in our own studies (Trauzettel-Klosinski et al 2006). Again, dyslexics showed normal reaction times for the pictograms and prolonged reaction times for reading words (Fig 2).

[figure not shown]

Figure 2:

*Magnetic activity during the reading of words and the naming of pictograms on the Magnetoencephalogram (MEG): In the pictogram task there is no difference between the groups, while in reading words the dyslexics show delayed responses compared to the control group. rw: rare words, fw: frequent words, pn: pictograms (from Trauzettel-Klosinski et al 2006).*

This led to the approach that dyslexic children might have a visual advantage if they were given pictographic/logographic rather than phonological tasks. This led to the plan that children who are dyslexic in an alphabetic language should learn a logographic language in order to possibly be as good as their classmates here.

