## **5. STUDY PROCEDURE AND RESEARCH METHODS**

### **5.1 study design**

The proposed study is a prospective clinical and pedagogic diagnostic and intervention study with dyslexic and normal-reading children entering 5th grade in the fall of 2018.

Pilot study: 3 children each with and without dyslexia.

Main study: 21 children each of the 4th and 5th grade with and without dyslexia.

- 1) Preliminary ophthalmological examination to exclude visual deficits.
- 2) Examination of eye movements during reading of alphabetical text and familiar pictograms on the SLO and eye tracker.
- 3) Examination of the further processing of the stimuli in the brain by means of MEG
- 4) Block teaching of Chinese language for 2 weeks during school vacations (24 school hours, 6-8 children per learning group)
- 5) Control examination of eye movements while reading alphabetical text and the newly learned Chinese characters on the SLO and eye tracker.
- 6) Investigation of the further processing of the stimuli in the brain by means of MEG

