## **9. INFORMATION ON THE STATISTICAL EVALUATION**

It is planned to analyze the data by means of an analysis of variance and to use non-parametric tests in case of non-normal distribution.

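### One headline question asks whether dyslexic children learn Chinese script as well as classmates, but the only analysis named tests for a difference and no criterion for similarity is given

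*Protocol*

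**What the plan says.** The Summary (section 1) sets out to investigate whether "German-speaking dyslexic children can learn the non-letter logographic Chinese script as well as their normal-reading classmates". Section 2.2, under the heading on processing of stimuli in the brain, repeats the idea: dyslexic children "should learn a logographic language in order to possibly be as good as their classmates here".

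The statistical section of the protocol (section 9) is one sentence: "It is planned to analyze the data by means of an analysis of variance and to use non-parametric tests in case of non-normal distribution". No equivalence or non-inferiority hypothesis, margin, interval criterion, significance level, power or sample-size rationale appears in the document.

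On size, the Summary states: "Twenty-four children each from 4th and 5th grade with and without dyslexia will be included in the study". Section 5.1 gives "Main study: 21 children each of the 4th and 5th grade with and without dyslexia" and "Pilot study: 3 children each with and without dyslexia".

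**The concern.** A statement that one group learns as well as another needs evidence that any deficit is small. An analysis of variance, or a rank test in its place, asks whether the data are incompatible with no difference. When such a test is not significant, the data may fit equality, a sizeable deficit, or both.

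If this question were answered with the named method alone, a smaller or noisier study would be more likely to give the favourable-looking result. What is at stake is the validity of one headline conclusion. The protocol's other aims are not affected.

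**Working it through.** **Question and method side by side.** The Summary and section 2.2 ask about similarity. Section 9 names methods whose null hypothesis is equality. Nothing in the protocol links the two.

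**Inputs from the protocol.** Main study 21, pilot 3, and 21 + 3 = 24, which agrees with the Summary. The wording does not settle whether these counts are per group or per grade within group. Per grade, the groups would be 2 × 21 = 42 in the main study and 2 × 24 = 48 in all. The pilot count names no grade in section 5.1, and 42 + 3 = 45 is not 48, so the smaller reading fits more easily. The larger one is possible if the pilot count is also per grade. Both are shown.

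**Assumptions (not in the protocol).** Two-sided 5% level (one-sided 2.5% for non-inferiority), equal groups, differences in SD units, no dropout, a plain two-group comparison, and a higher score meaning better learning. The 0.5 SD deficit is illustrative. The protocol gives no power calculation, so there is none to reproduce.

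**Step 1: precision.** Half-width of the 95% CI = t(0.975, 2n−2) × √(2/n).
- n = 21: 2.021 × 0.3086 = 0.62 SD
- n = 24: 2.013 × 0.2887 = 0.58 SD
- n = 42: 1.989 × 0.2182 = 0.43 SD
- n = 48: 1.986 × 0.2041 = 0.41 SD

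So with 21 per group, even an observed difference of exactly zero leaves a deficit of about 0.6 SD inside the interval.

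**Step 2: chance that the difference test misses a true 0.5 SD deficit.** Noncentral t with noncentrality 0.5 × √(n/2).

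| n per group | Noncentrality | Power | Missed |
|---|---|---|---|
| 21 | 1.62 | 35% | 65% |
| 24 | 1.73 | 40% | 60% |
| 42 | 2.29 | 62% | 38% |
| 48 | 2.45 | 68% | 32% |

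**Step 3: deficit that could be excluded with 80% power if the groups are truly equal.** Solve for the margin m at which P(T > t(0.975, 2n−2)) = 0.80, where T is noncentral t with noncentrality m × √(n/2).
- n = 21: 0.89 SD
- n = 24: 0.83 SD
- n = 42: 0.62 SD
- n = 48: 0.58 SD

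For a margin of 0.5 SD, the non-inferiority power is 35%, 40%, 62% and 68% in the same order. It is below 80% on either reading of the counts.

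**The case against.** The strongest reply is that section 9 is a general sentence about all the data, including eye movements and MEG, and that margins and intervals are often left to a statistical analysis plan, which may exist. An analysis of variance can also yield a group contrast with a confidence interval. This is fair as far as it goes, and it is why the method need not be dropped. It does not remove the mismatch: the protocol itself names the type of test, and that type, used as a test, cannot answer this question.

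Five stronger readings are tempting, and the protocol does not support them:
- **That non-significance will be read as equality.** No such rule is written. Section 2.2 does describe an earlier result as "In the pictogram task there is no difference between the groups", but this is a caption to a figure from a previous study whose analysis is not shown. It is not evidence of how this study will be judged.
- **That this is the primary question.** No question is labelled primary. Section 3.1 asks about local versus global processing and about using visual competence. Section 3.2 asks whether dyslexic children learn Chinese characters better than alphabetic ones, and a difference test suits that aim.
- **That a missed deficit would drive the offer of Chinese classes to dyslexic children.** Section 3.2 makes that offer depend on whether these children can learn Chinese at all, and section 8 sets no condition of equality for them either.
- **That a medium deficit would usually be missed.** This is true with 21 or 24 per group, but not with 42 or 48.
- **That only deficits of 0.8 to 0.9 SD can be excluded.** This too holds only on the smaller reading. On the larger one the figure is about 0.6 SD.

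**Conclusion.** The point holds in a limited form. One headline question is about similarity, the only named analysis tests for a difference, and the protocol gives no criterion by which a favourable answer could be reached. That conclusion rests on the text and does not depend on the illustrative numbers.

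The size of the problem depends on an unclear count. It is marked with 21 or 24 children per group and milder, though still present, with 42 or 48. The significance level, the 0.5 SD deficit and the absence of dropout are assumptions; dropout would widen the intervals.

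This should be fixed, but it does not undermine the study as a whole.

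**What to change.** In section 9:

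1. Keep analysis of variance (or its non-parametric substitute) for the difference-type aims.
2. For the similarity question, name a character-learning score. Report the dyslexic-minus-control difference with its 95% CI, adjusted for grade.
3. Claim that dyslexic children learn as well as classmates only if the lower limit lies above a margin justified in advance. Otherwise report the interval and state that equality is not shown. If no margin can be justified, reword the aim as estimation of the difference.
4. Clarify whether the counts are per group or per grade. Then state the deficit that the planned size can exclude with 80% power if the groups are truly equal: about 0.83 to 0.89 SD with 24 to 21 per group, or about 0.58 to 0.62 SD with 48 to 42.

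The cost is a short revision of the text, with no extra children or visits. The real effort lies in naming the score and justifying a margin, neither of which the protocol now provides. The claim also becomes harder to make.

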## **11. data privacy**

The data are collected on questionnaires or examination forms and stored in computer files. The data are stored in pseudonymized form immediately after collection. For this purpose, a code is assigned, and a list is kept that would allow the data to be traced.

The coding records and the coding list, together with the consent forms, are kept in a locked cabinet to which only the investigators have access. It will be made available to third parties only in the cases specified in the privacy consent form. The data will be kept for 10 years.  
Separate information sheet of the University clinic Tuebingen will be enclosed.

## **12. Education of the study participants**

Each subject and each patient with at least one parent will be informed in detail about the procedure of the study by the investigator before they give their consent. All subjects/patients and their parents are explicitly informed that they can terminate their participation, or the participation of their child, in the study at any time and without giving reasons. Only then do the study participants and their parents give their consent to the studies.

Compensation: The children will receive a voucher (books, visit to the cinema) worth 25 € after completion of the last examination, the parents will also receive an expense allowance of 25 €.

## **15. attachments**

information and consent sheet
